## Methods

### Design

The study is conducted at five sites in the cities of five countries in Central and Eastern Europe (Sofia, Bulgaria; Zagreb, Croatia; Skopje, Macedonia; Kotor, Montenegro; and Siret, Suceava County, Romania). In each country, the study is designed as a health-economic evaluation alongside a pragmatic randomized trial in two parallel groups, comparing newly implemented community-based recovery-oriented mental health care (CMHC) with CAU. Measurements will be performed at baseline (*t_0_*) and at 12 and 18 months after baseline (*t_1_* and *t_2_*, respectively). A Consolidated Standards of Reporting Trials (CONSORT) flow diagram of the study is shown in Multimedia Appendix 1.

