### Cost-Effectiveness Analysis

The CEA, with costs and WHODAS functioning as the primary outcomes, will be conducted in several steps.

First, WHODAS global functional disability will be computed using the scoring algorithm based on the item response theory as recommended by WHO [6]. This algorithm provides a per patient functional disability score between 0 and 100, with higher scores indicating greater disability.

Second, the sample characteristics at *t_0_* will be described to see if despite randomization, some baseline imbalances across conditions have occurred in prognostically relevant variables (ie, variables that are strongly correlated with the outcome). If this is the case, such variables will be used as covariates to make adjustments for the baseline imbalances. In the unlikely scenario where many potential confounders are found, covariate adjustments will be made more efficiently using inverse propensity score weighting, with w=1/p in the control group and w=1/(1-p) in the experimental group, where *w* is the weight and *p* is the propensity score (ie, the likelihood that a participant is in one condition rather than the other), and *p* will be estimated under a logistic model.

Third, dropout will be evaluated, and missing observations in WHODAS functioning at *t_1_* and *t_2_* will be imputed to permit ITT analysis. The imputation will be based on the predictors of outcome (for accuracy) and predictors of missing values (to adjust for possibly selective dropout). To handle missing data, single imputation using predictive mean matching embedded in nonparametric bootstraps of seemingly unrelated regression equations (SURE model) will be used. In a recent paper by Brand et al, single imputation nested in the bootstrap percentile method emerged as the method with the best statistical properties [20]. Predictive mean matching will be used to account for nonnormality of the data by imputing “real” observed values from similar cases instead of imputing regression estimates [21,22].

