Fourth, in the context of the economic evaluation, WHODAS global functioning must be dichotomized into a binary treatment response outcome. This is done because from an economics perspective, it is meaningless to relate hard currency (euro, which is measured at the interval level) to a health gain (measured at an “elastic” ordinal measurement level). In other words, for a health-economic evaluation, a “tangible” outcome on par with the hard currency required to generate that health outcome is needed in order to merit a meaningful analysis. In this analysis, a binary *treatment response* variable (1, improved; 0, not improved) would constitute such a hard outcome. For the main analysis, treatment response is defined when a patient has improved by 0.33 standard units or more. A change of 0.33 standard units is equivalent to a 6-point change on the WHODAS 0-100 scale. Thus, when a patient has improved 6 points or more, the patient is considered as a treatment responder (ie, treatment response=1 or else 0).

Fifth, to simultaneously evaluate both costs and outcomes, SURE models will be used. The SURE models will be baseline adjusted with baseline WHODAS functioning and cost as covariates or weighted with inverse propensity scores as needed. Because costs are nonnormally distributed, the SURE models will be bootstrapped (2500 times). When bootstrapping, one creates N times (in this case 2500 times) a new sample out of the original sample with replacement. This results in N different samples. Incremental cost-effectiveness ratios (ICERs) will be computed by dividing the between-condition differences in costs by the difference in effects (treatment responders). Thereafter, the scatter of 2500 bootstrapped ICERs will be plotted on the ICER plane. When most simulated ICERs fall into the north-east quadrant of the ICER plane (indicating that better health is achieved at higher costs), an acceptability curve will be graphed for decision-making purposes. The acceptability curve depicts the likelihood that the new health care system has acceptable cost-effectiveness relative to CAU given varying willingness-to-pay ceilings for gaining a QALY [23].

These health-economic evaluations will answer the question, “To what extent the newly implemented community-based recovery-oriented health care system has better patient-level outcomes with regard to WHODAS functioning?”

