### Cost-Utility Analysis

The methods for the CUA are the same as those for the CEA, with the exception that the incremental costs per QALY gained is the primary outcome. The QALYs will be computed from the EQ-5D-3L and will be based on the Slovenian VAS-based tariffs and the AUC method [9]. The Slovenian tariffs will be used in the absence of local tariffs for the participating countries, and hence, the Slovenian tariffs are deemed most representative. In the sensitivity analyses, alternative strategies for computing the QALYs will be used.

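### Baseline EQ-5D utility is not fixed as a covariate of the QALY equation; as written, it enters only if it is judged imbalanced

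*Protocol article*

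**What the plan says.** Three parts of the protocol article's Methods bear on this point.

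- **Covariates.** The fifth step of Cost-Effectiveness Analysis states: "The SURE models will be baseline adjusted with baseline WHODAS functioning and cost as covariates", with inverse propensity weighting as the alternative where needed.
- **Carry-over to QALYs.** Cost-Utility Analysis states: "The methods for the CUA are the same as those for the CEA, with the exception that the incremental costs per QALY gained" becomes the primary outcome. It adds: "The QALYs will be computed from the EQ-5D-3L and will be based on the Slovenian VAS-based tariffs and the AUC method". Under Design: "Measurements will be performed at baseline (*t_0_*) and at 12 and 18 months after baseline".
- **Imbalance check.** The second step of Cost-Effectiveness Analysis looks at whether "some baseline imbalances across conditions have occurred in prognostically relevant variables (ie, variables that are strongly correlated with the outcome"). It continues: "If this is the case, such variables will be used as covariates to make adjustments for the baseline imbalances". If many such variables are found, inverse propensity weighting is used instead. No criterion for imbalance is given.

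Baseline EQ-5D utility is not named as a covariate in Cost-Utility Analysis, Sensitivity Analyses or Analysis of Pooled Trial Data. The section on pooled data names no covariates for any model.

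**The concern.** The covariate pair suits the cost-effectiveness analysis, where WHODAS and cost are the baseline values of the two outcomes being modelled. Carried over unchanged, it no longer matches: the effect outcome is now the QALY, and its own baseline is utility. The mismatch matters more for a QALY than for most outcomes, because an area-under-the-curve QALY contains the pre-treatment utility as a component.

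Randomization and Masking specifies simple 1:1 randomization and mentions no stratification, and each site has 90 patients per arm. Chance differences in baseline utility are therefore to be expected. Baseline WHODAS removes only the part of such a difference that it shares with utility. The rest reaches the incremental QALYs, and from there each site's ICER and acceptability curve, which are meant to inform policy briefs.

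**Working it through.** **The plan's own figure.** The article gives no precision figure for QALYs. Its Table 1 concerns WHODAS and reproduces in all nine cells from n per arm = 2(1.96 + 0.8416)²/0.33² × [(1 + r₁,₂)/2 − r₀,₁²]. The worst case is 144.15 × (0.70 − 0.09) = 87.9, that is 88. At r₁,₂ = 0.4, raising r₀,₁ from 0.3 to 0.5 lowers the requirement from 88 to 65. The plan thus already relies on adjusting an outcome for its own baseline.

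**Inputs from the article.** Visits at 0, 1 and 1.5 years; area-under-the-curve QALYs; 90 per arm per site; 900 pooled (450 per arm).

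**Assumptions not in the article.** Utility SD 0.25. Correlation ρ between utilities at any two visits, 0.3 to 0.6. Correlation r between baseline WHODAS and baseline utility (absolute value), 0.3 to 0.6. Baseline WHODAS related to later utility only through baseline utility.

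**1. QALY weights.** (u₀ + u₁₂)/2 × 1 + (u₁₂ + u₁₈)/2 × 0.5 = 0.50u₀ + 0.75u₁₂ + 0.25u₁₈. Baseline takes 0.50/1.50 = one third. Discounting the last half-year at 3.5% gives 0.50, 0.742 and 0.242, so the share hardly moves.

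**2. Residual variance, in units of utility variance.**
- Var(Q) = 0.875 + 1.375ρ and Cov(Q, u₀) = 0.5 + ρ.
- After baseline utility: Var(Q) − (0.5 + ρ)².
- After baseline WHODAS: Var(Q) − r²(0.5 + ρ)².

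| ρ | r | Var(Q) | after utility | after WHODAS | SE ratio (utility/WHODAS) |
|---|---|---|---|---|---|
| 0.5 | 0.5 | 1.5625 | 0.5625 | 1.3125 | 0.655 |
| 0.6 | 0.3 | 1.7000 | 0.4900 | 1.5911 | 0.555 |
| 0.3 | 0.6 | 1.2875 | 0.6475 | 1.0571 | 0.783 |

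The SE reduction is therefore 22% to 44%. A second set of assumptions took baseline-to-follow-up utility correlation 0.3 to 0.5, between follow-ups 0.2 to 0.4, and r 0.3 to 0.7. The SE with WHODAS alone was then about 1.2 to 1.7 times the SE with utility.

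**3. Shift from chance imbalance, per site.**
- SE of the baseline difference: 0.25 × √(2/90) = 0.0373. 95% limit: 1.96 × 0.0373 = 0.073.
- Through the baseline term of the QALY alone: 0.5 × 0.073 = 0.037.
- In total with no adjustment at ρ = 0.5, slope 0.5 + ρ = 1.0: about 0.073.
- After WHODAS adjustment the fraction 1 − r² remains. At r = 0.5: 0.073 × 0.75 = 0.055.

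**4. Pooled.** The 95% limit is 1.96 × 0.25 × √(2/450) = 0.033. After WHODAS adjustment at r = 0.5: 0.033 × 0.75 = 0.025.

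**5. What the imbalance check recovers.** The article states no threshold, so a rule of adding utility when |t| > 1.96 was assumed. There were 4,000 simulated trials of 90 per arm for each of three correlation settings: baseline-to-follow-up 0.3, 0.5, 0.4; between follow-ups 0.4, 0.4, 0.3; r 0.5, 0.5, 0.3. Results are in utility SDs.

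| Adjustment | SD of QALY difference | Mean shift when baseline difference exceeds +1 SE |
|---|---|---|
| WHODAS only | 0.160–0.173 | 0.12–0.20 |
| Utility added only if imbalanced | 0.153–0.159 | 0.09–0.15 |
| Utility always | 0.108–0.125 | about 0 |

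**The case against.** The strongest reply is that the plan does provide for adjustment. The imbalance check belongs to the methods carried over, and baseline utility is an obvious candidate for it. A reader might infer that the cost-utility analysis never adjusts for baseline utility; that check shows otherwise. What stands is narrower. The check depends on the data and has no threshold. Run as a significance test, it recovers little precision and leaves most of the shift.

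Second, the carry-over cannot be wholly literal, since scoring and dichotomising WHODAS make no sense for QALYs. One could read the covariate rule as the baseline of each outcome, which would give utility and cost. That reading is reasonable, but the text does not say it, and two analysts could fit different models.

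Third, the article condenses a central Study Protocol that is not shown, and covariate lists are often settled there. That applies to the pooled and alternative-tariff analyses, where no covariates are stated and so nothing is stated wrongly. For the main cost-utility model, the article does state a covariate set and carries it over.

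Fourth, randomization leaves the QALY difference free of systematic bias, and the bootstrap already reflects the sampling error. This is correct and limits the point to precision and to chance error in the realised trial.

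Fifth, the size rests on assumed correlations. Any direct link from baseline WHODAS to later utility would shrink the gain.

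**Conclusion.** The point holds as a weakness of specification: baseline utility is not pre-specified in the QALY equation and enters only by a judgement of imbalance. The consequence is a wider QALY comparison and partial passage of chance imbalance into each site's result. With a utility SD of 0.25 and both correlations at 0.5, a 95%-limit imbalance leaves a shift of about 0.055 QALY per site, and about 0.025 pooled. An imbalance of one SE leaves about half of each figure. None of the SDs or correlations is given in the article.

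A reader might go further and infer that any baseline difference passes in full into the ICER, or that the QALY estimate is biased. The article does not support either: WHODAS adjustment removes part of the difference, the imbalance check may remove more, and allocation is random. No stated figure changes, because the trials are powered on WHODAS functioning and not on QALYs.

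**What to change.** State in Cost-Utility Analysis that baseline EQ-5D utility is a fixed covariate of the QALY equation, whatever imbalance is observed. Baseline WHODAS may stay: in the simulations the SD was nearly the same with both as with utility alone (for example 0.1248 against 0.1246). Keep baseline cost in the cost equation. For consistency, use the matching baseline value in each alternative-tariff or VAS analysis, and include baseline utility in the pooled QALY and net-benefit models.

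The cost is a sentence or two of text and one model parameter. The area-under-the-curve QALY already requires EQ-5D at baseline, so no data are added.

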### Cost-Utility Analysis

The methods for the CUA are the same as those for the CEA, with the exception that the incremental costs per QALY gained is the primary outcome. The QALYs will be computed from the EQ-5D-3L and will be based on the Slovenian VAS-based tariffs and the AUC method [9]. The Slovenian tariffs will be used in the absence of local tariffs for the participating countries, and hence, the Slovenian tariffs are deemed most representative. In the sensitivity analyses, alternative strategies for computing the QALYs will be used.

### Sensitivity Analyses

The analyses mentioned above will be subject to a series of sensitivity analyses to gauge the robustness of the main findings. Sensitivity analyses will be directed at several uncertainties. First, the health-economic evaluation in the main analysis is restricted to the health care system’s perspective, where the costs are confined to the health care costs incurred by mental health services. In the sensitivity analysis, the health care perspective will be broadened to include the out-of-pocket costs of the patients and their family members for informal copayments, traveling costs for trips to healthcare centers, and informal care. In addition, the costs and benefits stemming from changes in productivity losses will be included. These costs stem from sickness absence (absenteeism) and lesser efficiency while at work (presenteeism). Second, in the main analysis, the valuation of the EQ-5D health states (ie, the tariffs) will be based on the Slovenian tariffs. For the sensitivity analysis, the tariffs will also be based on the study by Greiner et al, which is representative of West European countries, but might be less valid for Central and East European countries [24]. In addition, for each of the participating countries, we will repeat the main analysis using the country-specific EQ-5D VAS. Third, extreme cost outliers in the data may exert a disproportional influence on the economic evaluation. In the sensitivity analysis, we will rerun the economic evaluation while winsorizing cost data (ie, replacing the top 10% highest costs by more modest costs corresponding with the 90th percentile) [25]. Fourth, the choice of the discounting rates may impact the outcomes of the health-economic evaluation and will therefore be varied between 1% and 5% for both the costs and QALY gains. In a sensitivity analysis, the main analyses will be repeated with an annual discounting rate of 3.5% for the effects and 4.0% for the costs, as per the Dutch guidelines for health-economic evaluation [26].

The sensitivity analyses will help to assess the robustness of the findings that were obtained under the main analysis and will enrich the main analysis by taking different perspectives.

### Analysis of Pooled Trial Data

One of the secondary goals of the RECOVER-E project is to support and develop on-site research skills and to strengthen collaboration between countries. Therefore, the health-economic evaluations will be carried out locally at each of the sites. Central analysis will also be conducted for the pooled dataset of 900 (5 × 180) participants. The pooled data will be analyzed using mixed linear models with random effects both at the patient and site levels (equivalent to individual participant data meta-analysis) or alternatively with design-based analysis for the data of participants clustered at sites. The pooled data analysis, which has greater statistical power to detect significant effects, will include WHODAS functioning (on the continuous scale), as well as treatment response (dichotomized) and EQ-5D QALY gains. Finally, the pooled data will allow for multilevel modelling of net monetary benefits as the outcome of interest, with net benefits defined as NB = E*λ- C, where NB represents the net benefits, E represents the effects, λ represents a varying willingness-to-pay value (in euro) for gaining one unit of E, and C represents the costs required for generating that one unit health gain.

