## Discussion

### General Considerations

This study will examine the cost-effectiveness of recovery-oriented community mental health care for patients with severe mental disorders (the intervention implemented in the RECOVER-E project) compared with CAU in Bulgaria, Croatia, Macedonia, Montenegro, and Romania. Health-economic evaluations will be conducted alongside hybrid effectiveness-implementation trials at each of the five sites. In addition, a pooled analysis will be performed combining all trial data. It is hypothesized that the shift toward deinstitutionalization using a locally adapted form of flexible assertive community treatment results in the reduction of health care costs by avoiding expensive emergency care or psychiatric hospitalization. At the same time, this intervention has a focus within service delivery on recovery goals, which is hypothesized to contribute to a greater sense of societal role fulfilment and participation in society among people with severe mental illness. It is not unlikely that patients receiving community care will show larger improvements in WHODAS personal and social functioning and EQ-5D health-related quality of life as compared with patients treated in hospital-based mental health care services.

Given the nature of the intervention, a pragmatic approach is chosen to implement and evaluate community mental health services. While this may affect internal validity (eg, due to the lack of allocation concealment and masking), the corresponding results may be more generalizable and applicable to routine practice settings [31]. Moreover, the proposed methodology includes some methodological solutions to combat threats to the internal validity of the trials (eg, inverse propensity score weighting when randomization appears to be suboptimal).

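### The acceptability curve is planned for a mainly north-east result and no other case, which omits the plan's own cost-saving hypothesis; its QALY ceiling in the responder analysis and the wording of C also need correcting

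*Protocol article*

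**What the plan says.** The fifth step of the Cost-Effectiveness Analysis section obtains the incremental cost-effectiveness ratio (ICER) by "dividing the between-condition differences in costs by the difference in effects (treatment responders"), so the effect is a binary WHODAS response. Then "the scatter of 2500 bootstrapped ICERs will be plotted on the ICER plane", with no condition attached.

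The acceptability curve does carry a condition. It is to be graphed "When most simulated ICERs fall into the north-east quadrant of the ICER plane", and nothing is said about other distributions. The same paragraph describes it as the likelihood of acceptable cost-effectiveness "given varying willingness-to-pay ceilings for gaining a QALY". The Cost-Utility Analysis section adopts these methods and changes only the outcome, to cost per QALY gained.

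Under General Considerations the article hypothesises that the new service "results in the reduction of health care costs by avoiding expensive emergency care or psychiatric hospitalization", and it expects better role fulfilment and functioning as well.

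The section Analysis of Pooled Trial Data plans multilevel models with "net benefits defined as NB = E*λ- C". There "λ represents a varying willingness-to-pay value (in euro) for gaining one unit of E", while "C represents the costs required for generating that one unit health gain".

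**The concern.** The article does not power the economic question. Its Sample Size Calculation section rests inference about cost-effectiveness on a probabilistic decision approach instead. The acceptability curve states that probability directly, as the share of bootstrap replicates in which λ·ΔE − ΔC exceeds zero. If the curve depends on where the replicates happen to fall, whether the reader gets that summary depends on the result.

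The condition also points away from what the trial expects, since lower cost with better outcome is south-east. A cheaper but less effective result (south-west) is not covered either, although there the answer turns on the willingness to pay.

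The other two matters concern units. A ceiling per QALY does not apply to an analysis whose effect is a responder. A cost per unit of gain, in euro per unit of effect, cannot be subtracted from E·λ, which is in euro. The evaluations are to be run locally at five sites, partly to build research skills, so different teams may follow the written wording differently.

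**Working it through.** The article gives no net benefit, willingness to pay or acceptability result, so there is no figure to reproduce. All values of λ, ΔE, ΔC and their standard deviations below are assumptions for illustration.

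**1. When is the north-east condition met?** Take ΔE as normal with mean 0.03 QALY and SD 0.025, independent of ΔC, which is normal with SD 600 or 1,200 euro. Then:

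- North-east share = P(ΔE > 0) × P(ΔC > 0), with P(ΔE > 0) = Φ(0.03/0.025) = Φ(1.2) ≈ 0.885.
- P(cost-effective) at λ = 20,000 is P(20,000·ΔE − ΔC > 0). The mean of this quantity is 600 − mean ΔC. Its SD is √(500² + 600²) ≈ 781 or √(500² + 1,200²) = 1,300.

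| Mean ΔC (euro) | North-east share (SD 600; 1,200) | Most north-east? | P(cost-effective) at 20,000 (SD 600; 1,200) |
|---|---|---|---|
| −800 (saving, as hypothesised) | 8%; 22% | no | 0.96; 0.86 |
| 0 | 44%; 44% | no | 0.78; 0.68 |
| +300 | 61%; 53% | yes | 0.65; 0.59 |

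For the first row with SD 600, the share is 0.885 × Φ(−800/600) ≈ 0.885 × 0.091 ≈ 0.08, and the probability is Φ(1,400/781) ≈ 0.96. The probability exists in every row, but the written condition calls for a curve only in the last.

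**2. South-west.** Take ΔE = −0.02 and ΔC = −500.

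- At λ = 20,000, net benefit is −400 + 500 = +100.
- At λ = 30,000, it is −600 + 500 = −100.

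The decision changes with λ, which is what the curve displays, yet no curve is provided for here.

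**3. Unit of the ceiling.** The effect in the CEA ICER is a responder and the ceiling named is per QALY. Suppose a responder gains 0.05 to 0.15 QALY. A ceiling of λ per QALY is then worth 0.05λ to 0.15λ per responder. Reading λ itself as the price of a responder overstates it by 1/0.15 ≈ 6.7 to 1/0.05 = 20 times.

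**4. Definition of C.** With C as incremental cost and ΔE > 0, net benefit is positive exactly when ΔC/ΔE < λ. With C read literally as ΔC/ΔE, it is positive only when ΔC/ΔE < λ·ΔE, so the threshold is multiplied by ΔE. At λ = 20,000:

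- ΔE = 0.05, ΔC = 400: correct 1,000 − 400 = +600; literal 1,000 − 400/0.05 = 1,000 − 8,000 = −7,000.
- ΔE = −0.02, ΔC = +500 (worse and dearer): correct −400 − 500 = −900; literal −400 − (500/−0.02) = −400 + 25,000 = +24,600.

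For a single participant who does not respond, E = 0 and a cost per unit gained does not exist.

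**The case against.** The strongest defence has four parts, and much of it stands.

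- **The article does not exclude other curves.** It says when a curve will be drawn and does not forbid one elsewhere. A reader might infer an explicit ban, or that uncertainty is hidden when the result is not north-east. The text supports neither, because all 2,500 replicates are plotted whatever the result, and a cloud lying wholly south-east already shows dominance. What remains is that no curve is committed to in the other cases, and that a straddling or south-west cloud cannot be turned into a probability at a given λ by eye.
- **The net benefit formula is right.** λ is defined for any unit of E, the models have patient-level random effects, and the Costing section builds total costs aggregated over time. An analyst using patient-level costs would reach the correct result, and the literal C could hardly be computed. A reader might infer that the pooled net benefit will come out with the wrong sign. The documents do not support that; the sign reversals above show only what the words would mean if taken literally.
- **The QALY phrase may be a general description.** It sits in a block that the CUA reuses, where it is correct, and the ceilings vary with no fixed threshold. A curve computed from responder replicates has a per-responder axis by construction. The 7- to 20-fold range therefore illustrates a possible misreading and is not a planned error.
- **These are not the only inferential output.** A reader might think so, but bootstrapped seemingly unrelated regressions, ICERs, the ICER plane and a series of sensitivity analyses are planned too.

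**Conclusion.** The point holds at moderate weight. Its main part is the curve's condition. As written, a curve is provided for a mainly north-east result only, although acceptability is defined everywhere and the plan's own hypothesis lies south-east. This follows from the text and needs no assumed numbers; the shares of 8% to 22% and 44% only show how easily the condition can fail while the probability of cost-effectiveness is high or uncertain.

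The QALY ceiling in the responder analysis and the verbal definition of C are errors of wording with a lesser practical risk. Nothing here affects the design, the data collection, the sample size or the estimators.

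**What to change.** Change three sentences.

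1. In the Cost-Effectiveness Analysis section, remove the quadrant condition. Present the acceptability curve, as the share of replicates with λ·ΔE − ΔC > 0 over a range of λ, together with the share of replicates in each quadrant, for every CEA and CUA whatever the distribution.
2. In the same section, define λ per additional treatment responder for the CEA, and keep the ceiling per QALY for the CUA.
3. In Analysis of Pooled Trial Data, keep the formula and define C as each participant's total cost over the same horizon as E.

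The cost is at most one extra graph per analysis, drawn from bootstrap replicates that are already planned. No new data are needed.
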